### Criteria for discontinuing or modifying allocated interventions {11b}

A participant may withdraw from the study for any reason at any time.

Permanent discontinuation from the study will take place if a participant:Requires oral corticosteroids for more than four consecutive weeks.Requires rescue treatment with a non-corticosteroid systemic agent (including but not limited to cyclosporine, methotrexate, mycophenolate mofetil, or azathioprine) or injectable or parenteral corticosteroid.Develops clinically significant abnormal laboratory results or adverse events (AEs), which rule out continuation of the study drug, as determined by the investigator.Becomes pregnant or plans to become pregnant during the study.Develops active TB during the study.Develops malignancy, except for localised non-melanoma skin cancers or carcinoma of the cervix in situ.Has a confirmed diagnosis of deep vein thrombosis, pulmonary embolus, or non-cardiac, non-neurologic arterial thrombosis.Takes prohibited medications when the continuation of the study drug would place the subject at risk, as determined by the investigator.Significantly non-compliant with study procedures, which would put the participant at risk for continued participation in the trial as determined by the investigator.

### Strategies to improve adherence to interventions {11c}

Participants will be provided with a study drug diary and asked to return drug containers to monitor adherence. The investigators will also remind participants of the treatment regimen at the end of every study visit.

### Relevant concomitant care permitted or prohibited during the trial {11d}

The following concomitant medications are permitted during the trial:Medications to treat chronic or acute conditions (with the exception of the prohibited medications listed below).Inhaled, ophthalmic drops and nasal corticosteroid formulations.Oral corticosteroids are permitted for rescue treatment, however may not exceed four consecutive weeks.Non-live vaccines.

The following concomitant medications or procedures are prohibited during the trial:Investigational product from another clinical trial.Concomitant systemic agents, including but not limited to methotrexate, cyclosporine, azathioprine, PDE-4 inhibitors, mycophenolate mofetil, biologic therapies and biosimilar versions of biologic drugs.Topical treatments for VLP other than the one prescribed in the study (Diprosone® OV).Intravenous, intramuscular and intralesional corticosteroids for VLP management.Live vaccines are prohibited during the study and up to 4 weeks following the last dose of the study drug.Medical and recreational cannabis.Traditional Chinese medicine.Strong CYP3A inhibitors or inducers.Elective surgery. If the subject must undergo emergency surgery, the study drug should be interrupted at the time of the surgery.

### Provisions for post-trial care {30}

Participants will return to standard clinic care post-trial.

### Outcomes {12}

The primary endpoint is the difference in mean change of GELP scores from baseline (week 8) to week 32 between deucravacitinib and methotrexate treatment groups.

The secondary endpoints will explore mean changes in:Vulvar Quality of Life Index (VQLI) [3] at weeks 8, 24 and 32Weekly use of topical corticosteroid, collected from the patient diary, and the number of 30-g tubes usedGeneral Health Questionnaire-28 (GHQ-28) [36] at weeks 8, 24 and 32Physician Global Assessment (PGA) [37] at weeks 8, 24 and 32Patient Global Assessment (PtGA) [37] at weeks 8, 24 and 32Immunological changes and expression of cytokines in serum (weeks 0, 8, 32) and tissue (selected participants) at weeks 0 and 32

### Participant timeline {13}

The participant timeline is shown in Fig. 1. A follow-up visit will take place 30 days (± 1 week window) after the end of the treatment visit (week 32) or after a premature discontinuation visit.

**Fig. 1 Fig1:**
[figure not shown]
Participant timeline

The schedule of activities for each study visit is shown in Fig. 2 (SPIRIT Figure).

**Fig. 2 Fig2:**
[figure not shown]
SPIRIT Figure outlining the schedule of activities for each study visit

### Sample size {14}

A total of 116 patients will be recruited. The sample size was determined using a *T*-test for independent means (STATA, version 17.0) [38]. We based the calculation of our sample size on a previous RCT comparing the mean change of GELP scores between two intervention groups after 24 weeks of treatment [7]. As the mean reduction in GELP scores in their intervention group of interest was equivalent to a standardised mean difference (SMD) of > 0.80 (large effect size based on Cohen’s* d* measure [39]), we used an SMD of 0.70 (moderate to large effect size) in our calculation. The result of the analysis indicated that a total of 58 participants, or 29 in each deucravacitinib and methotrexate group, will be required to provide 80% statistical power with a two-sided 5% significance level to detect an SMD of 0.70 in the mean change of GELP scores from baseline (week 8) to week 32 between the two intervention arms.

According to the literature, approximately 20–40% of VLP patients would require second-line treatment with systemic immunosuppression to control their disease [9, 13]. In the study by Fahy et al. [9], over 40% of patients required systemic therapy. Based on these, we estimated that half of the participants will be non-responders, and therefore, a total of 116 participants will need to be recruited to provide a sample size of 58 for both the deucravacitinib and methotrexate groups or 29 in each treatment arm.

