Vulvar lichen planus (VLP), the disease in focus in the presented study protocol, is a chronic inflammatory dermatosis characterised by erythema, erosions and hyperkeratosis on the vulva with possible vaginal involvement [6, 7]. It has a predilection for peri-/post-menopausal women in the fifth to sixth decades of life [8, 9]. The exact prevalence of VLP is unknown. It is estimated to be 3.7% from a study of 3350 women presenting to a vulvar clinic [8]. However, the actual prevalence in the general population is likely to be higher due to underdiagnosis.

Patients report significant vulvar pruritus, pain, burning sensation, discharge and dyspareunia, which leads to debilitating effects on sexual function and other aspects of life and reduces quality of life [4, 10, 11]. Ongoing disease activity can lead to vulvovaginal scarring and malignancy [10–12].

VLP is particularly difficult to treat. Unfortunately, despite the recognised disease sequelae and impact on quality of life, there are limited studies on direct therapy for VLP. The first-line treatment for VLP is potent topical corticosteroids, but approximately 20–40% of patients require second-line treatment with systemic immunosuppression to control their disease [9, 13]. Some of the systemic medications that have been used to treat VLP include prednisolone, methotrexate, mycophenolate mofetil, azathioprine, hydroxychloroquine, cyclosporine, rituximab, tildrakizumab, secukinumab, ustekinumab, adalimumab, tofacitinib and apremilast with varying results [14–26]. The best-documented agent appears to be methotrexate, with authors reporting a moderate efficacy and safety profile [15, 27–29]. However, these studies were either retrospective or small case series. There is no high-quality evidence, such as RCTs, to compare and guide second-line systemic treatments in VLP.

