## Discussion

High-quality evidence-directing therapy in VLP is lacking. Clinicians often base the choice of treatments for their VLP patients on clinical experience, anecdotal observations, case reports and small case series.

So far there have been very few RCTs exploring treatments for women with VLP. The RCT by Helgesen et al. compared vulvovaginal photodynamic therapy to topical corticosteroids [7]. Simpson et al. conducted the “hELP” RCT, investigating the utility of systemic therapy in addition to potent topical therapy [41]. The trial involved four arms: (1) prednisolone and clobetasol propionate 0.05%, (2) hydroxychloroquine and clobetasol propionate 0.05%, (3) methotrexate and clobetasol propionate 0.05% and (4) mycophenolate mofetil and clobetasol propionate 0.05%. However, the study was open-label and had to be stopped prematurely, as they did not reach the recruitment target of 40 participants in their initial 12-month pilot study [42]. Their commentary provided valuable insights into the potential challenges that investigators may face when running a clinical trial in patients with specific demographics and relatively rare conditions. Nevertheless, we are optimistic that these challenges can be overcome in our RCT, which we are conducting in a dermato-gynaecology centre with a large patient base and a high referral rate. Most recently, Skullerud et al. published the study protocol of their double-blinded RCT [20]. However, their study compared apremilast with placebo and not other systemic treatments. Hence, to our knowledge, this will be the first double-blinded RCT comparing systemic treatments in VLP patients.

The results of this RCT will provide clinicians with high-quality evidence to guide second-line systemic treatments in VLP and provide data on the safety and efficacy of deucravacitinib in the management of patients with this chronic and particularly difficult-to-treat condition.

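### The planning SMD of 0.70 between deucravacitinib and methotrexate rests on what is worded as a one-arm reduction in a trial of other treatments, and 29 per arm gives about 75% power for it, not 80%

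*Protocol article*

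**What the plan says.** Sample size {14} takes its effect size from a "previous RCT comparing the mean change of GELP scores between two intervention groups after 24 weeks of treatment". It reports that "the mean reduction in GELP scores in their intervention group of interest was equivalent to a standardised mean difference (SMD) of" more than 0.80, and continues: "we used an SMD of 0.70 (moderate to large effect size) in our calculation". The calculation is a t-test for independent means. It concludes that 58 participants, 29 per arm, give "80% statistical power with a two-sided 5% significance level to detect an SMD of 0.70". The role of the 0.70 is explicit: "to detect an SMD of 0.70 in the mean change of GELP scores from baseline (week 8) to week 32 between the two intervention arms". This matches the primary endpoint in Outcomes {12}, which is a between-arm difference in mean change.

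The Discussion says that the prior trial "compared vulvovaginal photodynamic therapy to topical corticosteroids". On the comparator, Background and rationale {6a} says: "The best-documented agent appears to be methotrexate, with authors reporting a moderate efficacy and safety profile". No section gives an expected GELP change for either study drug, an SD of change, or a smallest worthwhile difference.

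**The concern.** A between-arm difference is one arm's mean change minus the other's. The section cites what reads as the change in one arm and, after rounding down, uses it as the difference between two active arms. Nothing is subtracted for improvement on methotrexate, although methotrexate is described as moderately effective. The step down from more than 0.80 to 0.70 is not linked to any expected methotrexate response.

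If the planned effect is too large, the trial is more likely than stated to end without a significant difference. The Discussion expects the results to guide second-line treatment, so some readers could take such a result to mean that the two drugs work equally well.

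**Working it through.** **Inputs from Sample size {14}:** two-sided 5% level, 80% power, independent-samples t-test, SMD d = 0.70, 29 per arm, half of those recruited expected to be non-responders.

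**1. The plan's own figure.** The normal approximation is n per arm = 2(z₀.₉₇₅ + z₀.₈₀)²/d² = 2(1.960 + 0.842)²/0.70² ≈ 32.04, so 33. The exact noncentral t calculation gives 33.02, so 34. That is 66 to 68 randomised, or 132 to 136 recruited at 50% non-response. The stated 58 and 116 are not reproduced.

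Power at n = 29 comes from the noncentral t with 2n − 2 = 56 degrees of freedom and noncentrality d√(n/2). For d = 0.70 this is 0.70 × √14.5 ≈ 2.67, and power is 74.5% (76.0% by the normal approximation). Solving for 80% power at 29 per arm gives d = 0.749. Put the other way, d = 0.75 needs 28.9 per arm, so 29. The stated size therefore fits an SMD of 0.75. The document does not show how the mismatch arose.

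**2. From a one-arm change to a between-arm difference.** On a common SD, d(between) = d(deucravacitinib) − d(methotrexate). The documents give neither term for this trial, so the values below are assumptions. Deucravacitinib is set at 0.80, the lower bound quoted for the prior trial's arm.

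| Methotrexate change (SD, assumed) | Between-arm SMD | Power at 29 per arm | n per arm for 80% |
|---|---|---|---|
| 0.10 | 0.70 | 74.5% | 34 |
| 0.20 | 0.60 | 61.2% | 45 |
| 0.30 | 0.50 | 46.5% | 64 |
| 0.40 | 0.40 | 32.2% | 100 |
| 0.50 | 0.30 | 20.2% | 176 |

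At this bound, a difference of 0.70 leaves methotrexate only 0.80 − 0.70 = 0.10 SD of improvement.

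**3. Sensitivity to the bound.** The protocol says more than 0.80, so larger values are open. With 1.0 SD for deucravacitinib, a difference of 0.70 allows methotrexate 0.30 SD. With 1.2 SD it allows 0.50 SD. With 1.0 SD and methotrexate at 0.20 to 0.50 SD, the between-arm SMD is 0.80 to 0.50 and power is 84.9% to 46.5%.

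**4. Effect of the planned ANCOVA.** Suppose the model adjusts for baseline GELP, with equal variances and a baseline-to-week-32 correlation r (all assumed). The residual variance relative to that of change scores is then (1 + r)/2, and the detectable SMD of change is about 0.749 × √((1 + r)/2). For r = 0.3, 0.5 and 0.7 this is about 0.60, 0.65 and 0.69. Missing data would work in the other direction.

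**The case against.** The strongest reply is that the one-arm reading may be only loose wording. The prior trial is introduced as a comparison between two groups, and a standardised mean difference judged against Cohen's d is normally a between-group measure. The cited source is not at hand, so this cannot be settled, and a reader should not take it as established that a before–after figure was used. The point survives either way. If the figure was a between-arm contrast, it compared photodynamic therapy with topical corticosteroids, and neither is a randomised treatment here.

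Three further objections stand in part.

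- More than 0.80 is a lower bound, so the table in the working shows the unfavourable end.
- A reader might infer that a methotrexate response of about 0.10 SD contradicts the reason for choosing it. The documents do not support that. Explanation for the choice of comparators {6b} chose methotrexate as the best-documented agent and warns that the evidence is retrospective or from small series. A very small response would sit uneasily with the reported moderate efficacy, but that is tension, not contradiction.
- Statistical methods {20a} plans ANCOVA, which could be more precise than the t-test. That does not rescue the printed power, which the protocol attributes to a t-test with no stated correlation.

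A reader might also infer that a non-significant result would be worthless, or that the authors intend to claim equivalence. Neither follows. The missing-data section {20c} already commits to a pooled mean difference with a 95% CI, and no equivalence or non-inferiority claim is planned.

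**Conclusion.** The point holds in two parts.

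- **Effect size.** As worded, the justification does not support 0.70 for deucravacitinib versus methotrexate, because it cites a one-arm reduction from a trial of other treatments and makes no allowance for a methotrexate response. This shows that the effect has no stated basis in the document for this comparison. It does not show that 0.70 is false. The effect may be optimistic: power would be 61% to 20% if deucravacitinib improved by 0.80 SD and methotrexate by 0.20 to 0.50 SD on a common SD. Those figures are illustrative, and a larger deucravacitinib response makes them less severe.
- **Power statement.** This part needs no assumption about response. By the protocol's own test and error rates, 29 per arm gives about 74.5% power at an SMD of 0.70 and reaches 80% only at about 0.75.

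The trial can proceed, but the sample-size section should not stand as written.

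**What to change.** 1. Remove the prior trial's one-arm reduction as the justification for the effect size.
2. State the target as a between-arm difference in GELP points, chosen as the smallest worthwhile difference, with the SD of change from week 8 to week 32. Give the power of 29 per arm for that target.
3. Correct the power statement: with a two-sided 5% t-test, 29 per arm gives 80% power at an SMD of about 0.75 and about 74.5% at 0.70. If a gain from ANCOVA is to be claimed, state the assumed baseline correlation.
4. Add one sentence saying that a non-significant result will be interpreted through the 95% CI already planned and not reported as comparable efficacy.

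The cost is a rewritten sample-size paragraph, one added sentence and a less favourable stated power, with no extra patients. Keeping both 0.70 and 80% under the t-test would instead need 34 per arm, which is 68 randomised and 136 recruited at 50% non-response.

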## Assignment of interventions: allocation

### Sequence generation {16a}

The methotrexate and deucravacitinib treatment groups will have a 1:1 ratio of allocation, generated using appropriate statistical software.

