## Statistical methods

### Statistical methods for primary and secondary outcomes {20a}

The data will be presented as mean with standard deviation, median with interquartile range, or frequencies with percentages as appropriate. Analysis of covariance (ANCOVA) will be used to compare the mean change in GELP scores from baseline and week 32 between the deucravacitinib and methotrexate groups. Other endpoints will be analysed using independent samples *T*-test, Mann–Whitney *U* test, Fisher’s exact test, ANCOVA model or linear mixed effects model as appropriate. All statistical tests will be performed at a 0.05 level of significance.

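### The sample size does not follow from its stated inputs: 29 per arm gives about 74.5% power at SMD 0.70 under the stated t-test, not 80%

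*Protocol article*

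**What the plan says.** All of the design inputs are in the protocol article.

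- **Effect size** (Sample size {14}): "we used an SMD of 0.70 (moderate to large effect size) in our calculation". The section presents this as a step down from an effect above 0.80 in an earlier trial.
- **Test, level and endpoint** (same section): a t-test for independent means run in Stata 17.0, "with a two-sided 5% significance level to detect an SMD of 0.70 in the mean change of GELP scores", measured from week 8 to week 32.
- **Result** (same section): "a total of 58 participants, or 29 in each deucravacitinib and methotrexate group, will be required to provide 80% statistical power".
- **Recruitment** (same section): "we estimated that half of the participants will be non-responders", so 116 are to be recruited to give "a sample size of 58 for both the deucravacitinib and methotrexate groups or 29 in each treatment arm".
- **Allocation** (Sequence generation {16a}): "The methotrexate and deucravacitinib treatment groups will have a 1:1 ratio of allocation".
- **Primary analysis** (Statistical methods for primary and secondary outcomes {20a}): "Analysis of covariance (ANCOVA) will be used to compare the mean change in GELP scores". No correlation between baseline and outcome is given here or in the sample size section.

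**The concern.** The section names the test, the effect, the level and the power, and then reports a number that these do not produce. This is a wrong figure beside a full set of inputs, so nothing is being left to a longer document.

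Planned power and detectable effect are what an ethics committee, a funder and later readers rely on. If 29 per arm stands, the type II error at SMD 0.70 under the stated test is about 25%, not 20%, and a null result would be given more weight than the design supports. The margin below the earlier trial's effect also shrinks. The text implies a gap of 0.80 − 0.70 = 0.10, but at 29 per arm the effect detectable with 80% power is 0.749, which leaves 0.80 − 0.749 = 0.051. The recruitment target carries the same error.

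**Working it through.** **Inputs.** d = 0.70, two-sided α = 0.05, target power 0.80 and n = 29 per arm (Sample size {14}); 1:1 allocation (Sequence generation {16a}).

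**1. Attempt to reproduce the plan's figure.** For a two-sample t-test with n per arm, df = 2n − 2 and the noncentrality parameter is d√(n/2).

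- n = 29: df = 56; noncentrality = 0.70 × √14.5 = 2.666; critical t = 2.003.
- Power from the noncentral t = **0.745**. The normal approximation gives 0.760.

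Neither reaches 0.80, so the stated figure is not reproduced.

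**2. Sample size that the inputs require.**

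| n per arm | Power, exact t | Power, normal approximation |
|---|---|---|
| 29 | 0.745 | 0.760 |
| 32 | 0.787 | 0.7996 |
| 33 | 0.7997 | 0.812 |
| 34 | 0.812 | 0.823 |

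- Exact t: 34 per arm, 68 randomised.
- Normal approximation: n = 2(1.960 + 0.842)²/0.70² = 2 × 7.849/0.49 = 32.04, so 33 per arm, 66 randomised.
- Shortfall: 68 − 58 = 10, or 66 − 58 = 8.
- Recruitment at the plan's 50% non-response: 68/0.5 = 136, or 66/0.5 = 132, against 116.

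**3. Effect detectable at 29 per arm.** Solving for 80% power gives d = 0.749 by the exact t. At d = 0.75, 29 is the smallest n per arm that reaches 80% (power 0.801).

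**4. Other readings that might explain 29.**

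- *One-sided 5%:* needs 26 per arm, and 29 would give 83.8%. The text says two-sided in any case.
- *Dropout allowance:* 116 × 0.5 = 58 exactly, and 58 is described as the number required for 80% power, so no allowance is built in.
- *SMD 0.75:* gives 29 per arm by the exact t.
- *75% power at SMD 0.70:* the normal formula also gives 29 per arm.

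The last two match numerically. The article supports neither as the source.

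**5. Could the planned ANCOVA restore 80%?** If r is the correlation of week-8 GELP with change, adjustment reduces the residual variance by the factor 1 − r², so the effective SMD is 0.70/√(1 − r²). Setting this equal to 0.749 gives 1 − r² = (0.70/0.7487)² = 0.874, so |r| = 0.355. The article gives no r, so the following range is an assumption:

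| r | Power at 29 per arm |
|---|---|
| 0.1 | 0.749 |
| 0.2 | 0.762 |
| 0.3 | 0.784 |
| 0.4 | 0.815 |
| 0.5 | 0.856 |

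**The case against.** The strongest reply is that the primary analysis is an ANCOVA, so 74.5% is not the power of the planned analysis. If it adjusts for week-8 GELP, power with full follow-up will be at least about the t-test figure, and a correlation of 0.4 would already exceed 80%. This stands in part: 25% is close to an upper bound on the type II error at SMD 0.70 with complete data. It does not rescue the stated figure. The section says the calculation was a t-test, no correlation is offered, and randomising only those with GELP of 5 or more restricts the baseline range.

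Second, 33 per arm gives 79.97%, which most protocols would report as 80%, so the shortfall can fairly be put at 8. That is accepted, and the range of 8 to 10 reflects it.

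Third, the practical effect is modest. A detectable SMD of 0.75 is still below the earlier trial's 0.80. Achieved power also depends more on the assumed 50% non-response: the 20–40% quoted in the same section would give 116 × 0.2 = 23 to 116 × 0.4 = 46 randomised. This is true, and the estimand, type I error and participant safety are untouched. It argues for a short correction, but does not make the power statement correct.

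**Conclusion.** The concern holds. Under the stated t-test, SMD 0.70 and two-sided 5% level, 29 per arm gives 74.5% power (76.0% by the normal approximation), against a stated 80%. The plan is 8 to 10 randomised participants short of its claim. Equivalently, its 80% detectable effect is about 0.75.

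These results use only inputs stated in the article and assume that all 58 contribute week-32 data; losses would lower power further. The one unstated quantity that could close the gap is a baseline–change correlation of at least about 0.36 in absolute value, used through the ANCOVA. How 29 was obtained cannot be told from the article.

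**What to change.** First rerun the calculation and check which effect size and power were entered in Stata. Then correct the Sample size {14} section in one of these ways:

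1. State that 58 randomised participants give about 75% power for SMD 0.70.
2. State that they give 80% power for SMD 0.75. This suits the case where 0.75 is confirmed as the value used; otherwise the effect is being fitted to the sample size afterwards, and option 1 is cleaner.
3. Keep 80% at SMD 0.70, but base it on the planned ANCOVA and state the assumed correlation of week-8 GELP with change (at least 0.36 in absolute value), with its justification.

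Each is a text change to the protocol and to any other document that repeats the figure. No extra patients are needed; the cost is that a published figure becomes slightly less favourable, or that an assumption has to be defended. Only if 80% at SMD 0.70 by t-test is to be kept does the number have to rise, to 68 randomised and 136 recruited on the plan's 50% assumption, before any dropout.

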### Methods in analysis to handle protocol non-adherence and any statistical methods to handle missing data {20c}

The percentage of missing values for all the variables at each time point will be reported. For the primary outcome analysis, the missing values will be imputed using the multiple imputation method. Ten sets of imputed data will be created and analysed using the analysis method described for the primary outcome. The mean difference in mean change from baseline to week 32 between the methotrexate and deucravacitinib groups from the ten imputed analyses will be combined to obtain a pooled common mean difference and 95% CI. A complete case analysis will also be performed to assess the sensitivity of the magnitude and significance of the effects compared. All statistical tests will be performed at a 0.05 level of significance.

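### The stated 80% power does not follow from 116 recruited: the 58 is short on the plan's own inputs, and there is no margin for a non-responder rate below 50% or for attrition

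*Protocol article*

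**What the plan says.** All of the sizing is in the protocol article under Sample size {14}.

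- Recruitment: "A total of 116 patients will be recruited".
- Method: "The sample size was determined using a *T*-test for independent means (STATA, version 17.0"), and "we used an SMD of 0.70 (moderate to large effect size) in our calculation".
- Randomised number: "a total of 58 participants, or 29 in each deucravacitinib and methotrexate group", which "will be required to provide 80% statistical power with a two-sided 5% significance level to detect an SMD of 0.70".
- Step from randomised to recruited: the section cites 20–40% of patients needing second-line systemic treatment, adds one study with over 40%, and concludes from these that "we estimated that half of the participants will be non-responders, and therefore, a total of 116 participants will need to be recruited". Background and rationale {6a} gives the same 20–40%, as the share of "patients require second-line treatment with systemic immunosuppression to control their disease".

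Only women with GELP ≥ 5 after 8 weeks of topical steroid are randomised (Intervention description {11a}), so the non-responder rate fixes the size of the comparison.

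The sizing has no term for loss. Elsewhere the article provides for withdrawal at any time and lists grounds for permanent discontinuation ({11b}). For missing data, section {20c} says: "For the primary outcome analysis, the missing values will be imputed using the multiple imputation method".

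**The concern.** Three things in one calculation push the same way.

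1. The assumed rate is higher than the rates it is said to rest on. Because only non-responders are randomised, a higher rate lowers the recruitment needed, so this is the optimistic direction.
2. The 58 serves both as the number the power calculation calls for and as the number expected at randomisation. Nothing is left for a lower rate, for chance variation around 50%, or for missing week-32 scores.
3. The 58 does not reproduce from its stated inputs.

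The trial could recruit its 116 as planned and still have clearly less than 80% power for its only primary comparison. A null result between deucravacitinib and methotrexate would then be hard to interpret, and readers would judge it against a power the design never had.

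**Working it through.** **Inputs (Sample size {14}).** SMD 0.70; two-sided 5%; 80% power; independent-samples t-test; 1:1 allocation; 116 recruited; 50% non-responders. The article gives no attrition rate, so 10% and 20% below are assumptions.

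**Step 1: the plan's 58.**

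- Normal approximation: n per arm = 2(1.960 + 0.842)² / 0.70² = 32.04, rounded up to 33, or 66 in total.
- Exact t-test (noncentral t): n per arm = 33.02. At 33 per arm the power is 79.97%; rounding up gives 34 per arm, or 68 in total.
- At 29 per arm: noncentrality 0.70 × √(29/2) = 2.67. Power is 74.5% by the t-test and 76.0% by the normal approximation.
- The SMD detectable with 80% power at 29 per arm is 0.749, so 58 fits an SMD of 0.75, not 0.70. A one-sided test at SMD 0.70 needs 26 per arm, so that does not explain 29 either.

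The 58 does not reproduce. It is 8 to 10 short.

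**Step 2: from 58 to 116.** 58 / 0.50 = 116. This reproduces exactly, so it contains no margin.

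**Step 3: how many will be randomised.** With 116 recruited and non-responder rate p, the number randomised is Binomial(116, p).

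| p | Expected randomised | P(at least 58) |
|---|---|---|
| 50% | 58.0 | 0.54 |
| 45% | 52.2 | 0.16 |
| 40% | 46.4 | 0.02 |
| 30% | 34.8 | < 0.0001 |
| 20% | 23.2 | < 0.0001 |

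At a true 50%, the chance of reaching the 68 of step 1 is 0.04.

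**Step 4: power at the expected number.** Observed number = 116 × p × (1 − loss), split equally; two-sided t-test at SMD 0.70.

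| p | No loss | 10% loss (assumed) | 20% loss (assumed) |
|---|---|---|---|
| 50% | 58.0: 74.5% | 52.2: 69.9% | 46.4: 64.5% |
| 40% | 46.4: 64.5% | 41.8: 59.8% | 37.1: 54.5% |
| 30% | 34.8: 51.8% | 31.3: 47.4% | 27.8: 42.8% |
| 20% | 23.2: 36.3% | 20.9: 33.0% | 18.6: 29.5% |

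The correct reference for the cost of attrition is 74.5%, not 80%. At 50% non-response, 10% loss costs about 5 points (74.5 − 69.9) and 20% loss costs 10 (74.5 − 64.5). The further 5.5 points below 80% come from step 1.

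**Step 5: recruits needed.**

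| p | To randomise 58 | To randomise 68 |
|---|---|---|
| 50% | 116 | 136 |
| 40% | 145 | 170 |
| 30% | 194 | 227 |
| 20% | 290 | 340 |

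**Step 6: ANCOVA.** The primary analysis in section {20a} is ANCOVA, which reduces the requirement by the factor 1 − r², where r is the covariate's correlation with the outcome. With an assumed r of 0.35, 33.02 × (1 − 0.1225) = 28.98, so 29 per arm. With r = 0.30, 33.02 × 0.91 = 30.05, so 31 per arm. The article sizes on a t-test and states no r.

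**The case against.** The strongest reply is that the cited rates and the trial's rate are different quantities. The 20–40% describes need for systemic therapy among patients with VLP. The trial counts GELP ≥ 5 at a fixed 8 weeks among women who entered with GELP ≥ 5, at a specialist referral centre. Selection for moderate-to-severe disease could well give a rate above 40%, and one cited study already exceeds it. This stands. A reader might infer from the 20–40% that 50% is wrong, or that the number randomised will probably fall below 58; the documents support neither. They show only that 50% has no stated support beyond rates that lie mostly below it.

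A reader might also infer that the design cannot deliver 58 randomised. Under the plan's own 50% it delivers 58 on average. What can be said is that there is no margin.

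Nor does the article state that recruitment must stop at 116. It presents 116 as what is needed to provide 58, and the full protocol, which is not shown, may contain a recruit-until rule. The power figures in step 4 apply if 116 is in fact the number recruited, as stated.

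ANCOVA could recover some power. With an assumed r of 0.35, 29 per arm gives 80% and 26 per arm gives 75%. With r = 0.5, 26 per arm gives about 81%. This is a fair caveat on the t-test figures, but it does not rescue the text, which derives 58 from a t-test.

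Multiple imputation is no answer to attrition. It keeps every randomised woman in the analysis but does not in general restore the information lost with her week-32 score.

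Finally, the non-response assumption is openly stated, and a shortfall in the number randomised would be visible as it accrues. The issue affects precision and the stated power, not the validity of the comparison.

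**Conclusion.** The point holds in this form: the stated 80% power at SMD 0.70 does not follow from 116 recruited. By the plan's own t-test it is 74.5% in the best case the plan assumes (50% non-response, no loss), about 70% with an assumed 10% loss, and 64.5% at 40% non-response without loss.

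The 74.5% rests only on figures in the article. The other two depend on an assumed loss rate, or on carrying over a cited rate that may not transfer, and should be read as a sensitivity range rather than a forecast. All are for an unadjusted comparison; adjustment may raise them by an amount the article gives no means of judging.

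**What to change.** In Sample size {14}:

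1. Correct the power for 29 per arm to 74.5%, or state the covariate correlation that justifies 80% under ANCOVA and where it comes from.
2. Restate the power for the number expected to be randomised and observed, with a short table over non-response of 20–50% and assumed missing week-32 GELP of 0, 10 and 20%, as in step 4.
3. Say that the cited rates are not the trial's own week-8 non-response rate, and give whatever further basis there is for 50%.
4. Define the target as the number randomised, with 116 as a planning estimate of the recruitment it will take.

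The cost is wording and a less favourable stated power. If the sponsor chooses to hold a randomised target, recruitment may take longer: at 40% non-response, 145 recruits for 58 randomised or 170 for 68. That is a real burden at one centre, in a disease where the Discussion reports that an earlier trial stopped after missing a target of 40. Enrolling more is the sponsor's choice; correcting the stated power does not depend on it.
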